### Intervention

#### Pedometer

In week 1, participants in the intensive intervention group (A) and the pedometer group (B) arrive for their second visit at the health care center. They are offered a pedometer (YAMAX; model Yamax Digiwalker SW 200: Yamax Corporation, Tokyo, Japan), instructions for how to use the pedometer, how to record their daily steps and to set a daily step goal on a website (www.steg.se, Select Wellness AB, Stockholm, Sweden). The participants register steps daily in a diary, and are recommended to enter them onto the website weekly. Non-ambulant activities such as biking and swimming are translated into steps by a simple calculation (each 30 min of activity, regardless of intensity, gives 3500 steps). On the website a “healthy goal” of minimum 7000 step per day is depicted as a reference [47]. The participants are asked to decide on individual goals after the first week of wearing the pedometer. If a pedometer stops working or gets lost the participants are encouraged to pick up a new pedometer at the health care center or a new pedometer is sent by post.

#### Group counseling

Group A participants are offered 12 group meetings (Fig. 2) over two years’ time, with the majority of meetings being held in the first six months. The group meetings include a 30 min walk and 60 min group consulting and are steered by a health professional trained in physical activity promotion and familiar with models and techniques for behavior change. A workbook developed for the project, based on the Health Belief Model, the Stages of Change Model and Social Cognitive Theory is used. The content of the group counseling program and the behavior change techniques used is shown in Fig. 3. The order of the content may shift depending on holidays, season or other concerns that arise.

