Advising physical activity is both cost-effective and feasible in primary care [20, 21] and promotion of physical activity should serve as a basis in diabetes care [1, 22]. The Board of Health and Welfare (Socialstyrelsen) in Sweden gives high priority to physical activity in diabetes care and since 1999 strongly recommends primary care to provide advice and support for individuals with diabetes as well as for individuals with increased risk for developing diabetes [23, 24]. Given the low number of people with diabetes being sufficiently active, the promotion of physical activity in the Swedish diabetes care is not satisfactorily effective today and needs to be improved [25].

In the literature, a number of methods reinforcing physical activity promotion in primary care have been evaluated and shown to be effective. The World Health Organization put emphasis on primary care to encourage and support people to take better care of their own health and to use evaluated tools and technology for this purpose [26]. Pedometers have been helpful in increasing physical activity levels and in improving metabolic parameters in patients with diabetes in several previous studies [27–29]. Pedometers have also been efficient in increasing the number of steps with a subsequent improvement in blood pressure even in already healthy individuals [30]. An advantage with pedometers is their efficiency in increasing the motivation to be more active and less sedentary on a daily basis, which is especially important for metabolic control and in lowering blood pressure. Well-planned group counseling sessions led by health professionals have also been shown to be effective in reducing diabetes risk in several previous interventions [28, 31–33]. The group setting offers social support and a pronounced opportunity for participants to share experiences, encouragement and to strengthen change. Group education is emphasized in the Swedish diabetes care [23, 24] but is today used by only 24 % of primary care units [25].

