**Fig. 2 Fig2:**
[figure not shown]
Time frame for Sophia Step Study. Time points for intervention components (grey) and data collection (black) for all groups. *Including blood samples, anthropometric and physical activity measurements and questionnaires. More details are depicted in Table 1

Sophia Step Study started with a pilot group in March 2013, entailing 8 participants in group A and 6 in group C. The pilot revealed compliance to the protocol and ability to recruit and the first participants were recruited in November 2013. The plan is to have 310 participants completed the intervention in 2020.

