### Sample size and planned statistical analysis

The sample size calculation assumed 80 % power and was calculated drawing on previous literature [14, 66] by statistical power analysis. To detect a difference of > 0.6 mmol/mol in HbA_1c_ with a standard deviation of 1.2 % at 12 months between group A and B and between group A and C we need 56 per group. Taking account the compliance and drop-out (30 %) and patients which decline participation (20 %) we need in group A 100 patients, in group B 100 patients and in group C 110 patients.

The study will be evaluated with both quantitative and qualitative methods and a cost-effectiveness analysis will be performed. The CONSORT 2010 statement will be used for description and analysis [45]. Data will be analyzed following the Intent-to-treat approach (ITT). Descriptive statistics will be used to describe the study population at baseline. The study data will be examined for outliers, normality and missing data. Potential confounders as (e.g. BMI at baseline, gender and age) will be used if there are differences at baseline.

Un-paired and paired tests, correlation coefficients as well as ANOVAs will be used to assess the bivariate effects of the interventions and to analyze within-group and between-group differences and changes. In addition, logistic regression models and/or cluster analyses will be performed to analyze issues related to dose–response and responder characteristics. SPSS 22 (SPSS Inc., Chicago, IL, USA) will be used for the statistical analysis.

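### Only arm A is treated in counselling groups, yet both powered contrasts (A vs B, A vs C) are sized and tested as if all patients were independent; any positive intra-group correlation makes the standard errors too small.

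*Protocol article*

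**What the plan says.** Under Procedure and timeline, individual patients are randomised to three arms by closed envelope, stratified by gender. Under Group counseling, only arm A is offered 12 group meetings over two years, steered by a health professional: "The group meetings include a 30 min walk and 60 min group consulting". The order of the content may vary with season and other circumstances. Arm B has a pedometer and website, and arm C has usual care. The Background gives the reason for group delivery: "The group setting offers social support and a pronounced opportunity for participants to share experiences".

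Under Sample size and planned statistical analysis, the calculation is a plain two-group one: "The sample size calculation assumed 80 % power", "To detect a difference of > 0.6 mmol/mol in HbA_1c", "with a standard deviation of 1.2 % at 12 months", and "between group A and B and between group A and C we need 56 per group". It uses no intra-group correlation or design effect. The analysis is described as follows: "Un-paired and paired tests, correlation coefficients as well as ANOVAs will be used to assess the bivariate effects of the interventions". No term for counselling group appears. The cluster analyses mentioned in the same section concern dose-response and responder characteristics and do not adjust for treatment groups. The Limitations section discusses shared staff but not this point.

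**The concern.** Patients who walk together, share a leader and are meant to support one another may end up with more similar outcomes than patients in different groups. Arms B and C have no such groups, so the design is partially nested: clustered in one arm and independent in the other two. Un-paired tests and ANOVA estimate the variance of the arm A mean as though its patients were independent. If the intra-group correlation is positive, that variance is understated, intervals are too narrow and the stated power is too high.

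Arm A is in both powered contrasts and carries the superiority hypothesis, so the problem falls on the trial's main claim. B vs C is not affected by the counselling groups.

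**Working it through.** **Inputs from the Protocol article.** Difference 0.6, standard deviation (SD) 1.2, power 80%, 56 per group, allowances of 30% and 20%, planned arms of 100, 100 and 110.

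**Assumptions.**
- Two-sided alpha 0.05 (no alpha is stated).
- 0.6 and 1.2 are on one scale. They are printed in mmol/mol and in %, which is a separate matter.
- Counselling groups of m = 8 with fixed membership, and intra-group correlation (ICC) 0.02 to 0.05. The text states none of these.

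**1. The plan's own figure, with independent patients.**

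n per group = 2 × (1.96 + 0.8416)² × (1.2/0.6)² = 62.8, so 63 rather than 56. At 56 per group, 0.6/(1.2 × √(2/56)) = 2.646 and power = Φ(2.646 − 1.96) = 75.4%. The inflation does reproduce: 56/(0.7 × 0.8) = 100.

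**2. Clustering in arm A only, equal arms.**

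- Design effect in A: DE = 1 + (m − 1) × ICC
- True SE / naive SE = √((DE + 1)/2)
- Actual type I error of the naive test = 2 × (1 − Φ(1.96 / SE ratio))

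| m | ICC | DE | SE ratio | Type I error |
|---|---|---|---|---|
| 8 | 0 | 1.00 | 1.000 | 5.0% |
| 8 | 0.02 | 1 + 7 × 0.02 = 1.14 | √(2.14/2) = 1.034 | 5.8% |
| 8 | 0.05 | 1 + 7 × 0.05 = 1.35 | √(2.35/2) = 1.084 | 7.1% |

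The naive SE is too small by 1 − 1/1.034 = 3.3% to 1 − 1/1.084 = 7.7%.

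**3. Power for A vs B with 70 per arm analysed** (100 less 30%; the 20% is taken as refusals before randomisation).

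Power = Φ(0.6 / (1.2 × √((DE + 1)/70)) − 1.96)

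- ICC 0: Φ(2.958 − 1.96) = 84%
- ICC 0.02: Φ(2.860 − 1.96) = 82%
- ICC 0.05: Φ(2.729 − 1.96) = 78%

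For A vs C with 70 and 77 analysed, the same steps give 85.7%, 83.2% and 79.5%. If only 56 per arm remain, A vs B power is 75.4% without clustering and 68.5% at ICC 0.05.

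**4. Number needed for 80% power.**

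n per arm = (1.2 × 2.8016/0.6)² × (1 + DE): 63 at ICC 0, 68 at 0.02 and 74 at 0.05.

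**5. Sensitivity to group size.**

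If 30% drop-out shrinks each group from 8 to 8 × 0.7 = 5.6, DE is 1 + 4.6 × 0.02 = 1.092 to 1 + 4.6 × 0.05 = 1.23. Type I error is then 5.5 to 6.3%, and A vs B power at 70 per arm is 82 to 80%. Over m from 6 to 12 and ICC from 0.01 to 0.10, at 56 per arm, the SE ratio runs from 1.01 to 1.25 and type I error from 5.3 to 11.5%.

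**The case against.** The strongest reply is that the article condenses a fuller plan, lists families of tests for many outcomes, and fixes no single primary model. A random effect could reasonably be left to the full protocol or SAP. That limits the point but does not remove it: the article names tests and a sample size, and these do not fit the delivery it describes.

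Four further objections stand.

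- **The correlation may be zero.** Group meetings are one component beside pedometers, prescription and individual counselling, and HbA1c is a laboratory value. The Background passage argues for group support in general and is no evidence of correlated HbA1c. A reader might infer that the standard errors are certainly too small; the documents support this only if the correlation is positive.
- **Group size and stability are unknown.** A reader might take the pilot ("entailing 8 participants in group A and 6 in group C") as showing groups of 8. That is the pilot's enrolment in arm A, and nothing says these patients formed one counselling group. Nor does the text say whether groups are closed or rolling.
- **Type I inflation is conditional.** With individual randomisation, if the treatment changes nobody's outcome, group delivery adds no correlation and the test keeps its level. Inflation needs group effects that differ but average to zero.
- **Planned enrolment absorbs much of the loss.** A reader might infer that 80% power is eroded directly by clustering. No stated sample size supports that starting point: 56 per group gives 75.4% before any clustering, and 70 per arm gives 84%.

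**Conclusion.** The point holds in conditional form. The mismatch between group delivery in arm A and an analysis of independent patients is in the text, and it affects both powered contrasts. Its direction is known for any positive correlation; its size is not.

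On the assumptions of fixed groups of 8 and a correlation of 0.02 to 0.05, the effect is modest: a standard error 3 to 8% too small and a loss of roughly 2 to 6 percentage points of A vs B power at 70 per arm. The type I figure of 5.8 to 7.1% also requires group effects that vary around zero. The upper value of 11.5% needs groups of 12 and a correlation of 0.10, neither of which the documents support, so it marks the edge of a range and is not an expectation.

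That 56 does not follow from its own inputs, and that the difference and SD carry different units, are separate defects and are not caused by clustering.

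**What to change.** 1. Record the assigned counselling group for every arm A patient, whether or not they attend. Session attendance is already collected under Fidelity criteria.
2. Analyse A vs B and A vs C with a partially nested mixed model: a random group effect in arm A only, arm-specific residual variance, and small-sample degrees of freedom. The last matters because 100 patients in groups of 8 would make only about 12 or 13 groups. If groups are not closed, use a multiple-membership version.
3. State how groups are formed and whether membership is fixed, and report the estimated intra-group correlation.
4. Restate the power with an assumed group size and correlation. This need not mean enrolling more patients.

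The cost is one recorded variable, some model wording, and slightly wider intervals for contrasts with arm A. Group membership is easiest to capture while groups are being formed. Without it, the correlation can be neither estimated nor ruled out.

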**Fig. 3 Fig3:**
[figure not shown]
Group counseling program for group A with the content and the behavior change techniques

#### Person-centered individual counseling

Group A participants are offered individual consultations with their diabetes specialist nurse at 9 occasions. The nurses are trained in MI and are using an MI-spirit in their consultations. The consultation takes place concurrently with the study measurements and the health outcomes from the measurements and the number of steps taken recently serves as a basis for these talks. Moreover, the nurse is, during one of the first MI-talks prescribing physical activity according to the method FaR [35]. The nurse also informs participants about the opportunities that follow a prescription, such as subsidies to gyms and sport clubs and trained staff at certain sport clubs. The prescription is followed up yearly. All in all, the meetings take 45-60 min each.

#### Usual care

The control group (C) receives diabetes care as usual, except for the extra measurements included in the study. Usual care consists of seeing a diabetes specialist nurse and a general practitioner at least once a year and receiving lifestyle advice, including advice on physical activity. Depending on the metabolic status of the patient there might be consultations with both the nurse and/or the general practitioner more often. The number of consultations made will be recorded for each participant. A physical activity prescription might also be issued as a part of usual care, but not in a systematic way.

### Theoretical framework

It is widely recommended that program design should be based on a theory and the behavior change techniques used should be depicted to improve evidence synthesis [21, 43, 48]. The theoretical framework underpinning the two interventions in Sophia Step Study is the Health Belief Model, the Stages of Change Model and the Social Cognitive Theory [49]. Both the multi-component intervention (group A) and the pedometer intervention (group B) are using several behavior change techniques based on the CALO-RE taxonomy [48].

Based on these theories various intervention components were chosen to offer flexibility; to adjust to individual differences and preferences and to strengthen change. A conceptual framework visualizing the intervention program is depicted in Fig. 4.

**Fig. 4 Fig4:**
[figure not shown]
Conceptual framework of Sophia Step Study. The conceptual framework depicts the underlying theories, the intervention components with the behavior change techniques used and the expected outcomes for the two intervention groups

### Outcome measures

Measurements are made on all participants at week 0, 8, 12, 16, 24, month 9, 12, 18 and 24. The primary outcome variable is HbA_1c_. Health outcomes and measurement time points are summarized in Table 1. The measurements are planned to be performed within ± 2 weeks and notes are made if they are made sooner or later than this.

**Table 1 Tab1:** Outcome parameters and time points for measurements for all groups in Sophia Step Study

Variables	Baseline	Trial	Trial	Trial	Trial	Trial	Trial	Trial	Trial
		w. 8	w. 12	w. 16	6 m	9 m	12 m	18 m	24 m
**Biomarkers**									
HbA_1c_ (mmol/mol)	✓		✓		✓		✓		✓
Plasmaglucose (fasting) mmol/l	✓		✓		✓		✓		✓
Triglycerides (mmol/l)	✓		✓		✓		✓		✓
LDL (mmol/l)	✓		✓		✓		✓		✓
HDL (mmol/l)	✓		✓		✓		✓		✓
Total Cholesterol (mmol/l)	✓		✓		✓		✓		✓
Free fatty acids (mmol/l)	✓		✓		✓		✓		✓
Insulin (mU/l)	✓		✓		✓		✓		✓
IGF BP1 (μ/l)	✓		✓		✓		✓		✓
ApoA1 (g/l)	✓		✓		✓		✓		✓
ApoB (g/l	✓		✓		✓		✓		✓
C-peptid (pmol/l)	✓		✓		✓		✓		✓
**Anthropometry**									
Weight (kg)	✓	✓	✓	✓	✓	✓	✓	✓	✓
% Body fat	✓	✓	✓	✓	✓	✓		✓	✓
Height (cm)	✓						✓		
BMI (kg/m^2)^	✓	✓	✓	✓	✓	✓	✓	✓	✓
Waist circumference (cm)	✓	✓	✓	✓	✓	✓	✓	✓	✓
Sagittal Abdominal Diameter	✓		✓		✓	✓	✓		✓
Resting pulse and blood pressure	✓	✓	✓	✓	✓	✓	✓	✓	✓
**Physical activity**									
Physical activity level (counts/min)	✓				✓		✓	✓	✓
Resistance training									
Resistance training and hand grip strenght	✓		✓		✓	✓	✓	✓	✓
**Questionnaires & Health Measures**									
Demographic data	✓								
Smoking and snuffing habits	✓								✓
Dietary habits, FFQ	✓						✓		✓
Drinking habits	✓				✓		✓		✓
Stress and working conditions	✓		✓		✓		✓		✓
EQ-5D 3L	✓		✓		✓		✓		✓
Overall health and sleep	✓		✓		✓		✓		✓
IPAQ-short	✓		✓		✓		✓		✓
Social support for exercise	✓		✓		✓		✓		✓
Self-efficacy for exercise	✓		✓		✓		✓		✓
Neighborhood environment	✓		✓		✓		✓		✓
HADS	✓		✓		✓		✓		✓
PSS	✓		✓		✓		✓		✓
Swe-PAID-20	✓		✓		✓		✓		✓

#### Biomarkers

Measurements include fasting blood samples on HbA_1c_ (mmol/mol), plasma glucose (mmol/l), triglycerides (mmol/l), LDL (mmol/l), HDL (mmol/), total Cholesterol (mmol/l), free fatty acids (mmol/l), Insulin (mU/l), IGF BP1 (μ/l), Apolipoprotein-A1 (g/l), Apolipoprotein B (g/l) and C-peptid (nmol/l). HbA1c, haemoglobin A1c (ref < 5.2 %) is determined with immunologic MonoS method, Unimate (Roche Diagnostics, Basel, Schweiz). To convert HbA1c MonoS into HbA1c (DCCT) NGSP (National Glycoprotein Standardization Programme) the formula, NGSP = 0.92*MonoS + 1,33 is used. Plasma glucose are determinedwith a glucose oxidase method, total Cholesterol and triglycerides are determined by using enzymatic method, LDL and HDL are determined by using a homogeneous method, Apolipoprotein-A1 and Apolipoprotein B are determined by using turbimetric method and C-peptid are determined by using immunometric method using two monoclonal antibodies and detection with electrochemiluminiscense using a Modular E system (Beckman Coulter, Inc.). Serum insulin concentrations are determined with RIA-kits purchased from Pharmacia & Upjohn, Stockholm. IGFBP-1 concentrations in serum are determined by RIA according to the method of Póvoa et al. [50]. Samples are saved for later free fatty acid analyses.

#### Anthropometry

Anthropometric measurements include weight and percentage body fat using Tanita digital scale (Model TBF-300A, Arlington Heights, IL). Weight is measured with light clothes, no shoes to the nearest 0.1 kg. Height is measured at the first visit by use of a calibrated stadiometer to the nearest centimeter. Waist circumference is measured with SECA 201 tape, horizontal around the waist 2 cm above the umbilicus. Sagittal abdominal diameter is measured with the subject in a supine position with the knees expanded at the level of the umbilicus using a Holtain-Kahn abdominal caliper (Holtain, Ltd., Crosswell, Crymych; Dyfed, UK). Resting pulse and blood pressure is measured with Omron M6 Comfort.

#### Objectively measured physical activity

To objectively assess total physical activity as well as sedentary time and time spent in different intensities the ActiGraph GT1M accelerometer (ActiGraph, Pensacola, FL) will be used. The participants are asked to wear the accelerometer placed on the back all wakening hours for seven consecutive days. The accelerations are sampled at 10 Hz i.e. 10 times per second and data is summarized over one minute and outputted as numerical counts. Total physical activity is expressed as total counts and steps per day. Time spent sedentary and in different intensities is derived from established cut-points according to Freedson (1998) and Matthews (2005 and 2008) [51–53].

#### Resistance training

Initiation of regular resistance training is reported contemporary with the measurement. Hand grip strength is measured as a proxy for overall muscle strength [54]. Hand grip strength is measured in kilograms using the hand-held Saehan Hydraulic Hand Dynamometer, model SH5001 (former Jamar) (Saehan Corporation, Masan, South Korea).

#### Questionnaires

A web-site delivered questionnaire is e-mailed to the participants at baseline, week 12, and at 6, 12 and 24 months. The questionnaire takes 30-40 min to complete, incorporates several validated questionnaires and some study specific questions including demographic and lifestyle characteristics that aims to evaluate diet, physical activity, motivational circumstances to be physically active, overall health and well-being and problem areas in diabetes.

*Demographic data* are collected by study specific questionnaire with items on civil status, having children under 18, caring for relatives, educational level and income.

*Smoking and snuffing habits* are measured using questions on current and previous habits and the dose.

*An indication of dietary habits* is measured by a Food Frequency Questionnaire (FFQ) developed and validated by The Swedish National Food Agency. This questionnaire is recommended to use in Swedish populations for its validity and reproducibility and for comparable reasons [55].

*Drinking habits* are assessed by two items based on the amount and regularity of alcohol consumption [56].

*Stress and working conditions* are measured by 4 items on over-time, paid overtime, having subordinates and perceived work security.

*Health outcome* is measured using The EuroQol (EQ-5D 3L) that includes questions on mobility, hygiene, daily activities, pain/ discomfort and anxiety/depression. Within the particular EQ-5D dimension the responses are within three levels of severity; no problems, some or moderate problems and extreme problems. The questionnaire also measures overall health status on a vertical visual analogue scale where 0 indicates worst imaginable health and 100 best imaginable health [57]. An approval to use the instrument in the current project is received from The EuroQol group.

*Overall health and sleep* is measured by a 1-100 scale for health condition where 0 is worst possible and 100 is best possible. One question on difficulties falling asleep and one question on sleep quality.

*Subjectively assessed physical activity* is measured with The International Physical Activity Questionnaire (IPAQ), a self-administered 7-item questionnaire that evaluates the frequency and duration of walking, moderate- and vigorous-intensity physical intensity, and minutes spent sitting during the past week [58].

*Social support for exercise* is measured with Physical Activity Social Support (PASS) first developed by Sallis et al. [59]. The PASS examines general support (1 item), friend (2 items), family (2 items) and colleagues support for exercise. PASS is using a 4-point Likert response scale (1 = strongly agree to 4 = strongly disagree).

*Self-efficacy for exercise* is measured with the 5-item scale The Self-Efficacy for Exercise Scale. It assess one’s confidence to continue exercising when feeling tired, being in a bad mood, not having time, being on vacation and at bad weather [60].

*Neighborhood environment* is assessed by the scale Neighborhood Environment developed by Mujahid et al., 2007 and using a 5-point responses (1 = strongly agree to 5 = strongly disagree) [61]. In this study 17 items about abilities to undertake exercise and walking, availability of foods, safety and social environment are used.

*Depression and anxiety* is measured with The Hospital Anxiety and Depression Scale (HADS): HADS is a 14 item questionnaire consisting of two subscales; depression and anxiety, with seven items each. The items are graded on a four-point Likert scale ranging from 0-3. The total score ranges from 0-21 for the HADS depression scale and ranges from 0-21 for the HADS anxiety scale [62].

*Stress* is measured with The Perceived Stress Scale (PSS) which is a 14- item questionnaire used to measure how stressful different situations in one's life are perceived (Cohen et al. 1983). The items are graded on a five-point Likert scale. The total score for PSS ranges from 0-56. Eskin et al., 1996 have psychometrically tested the Swedish version of PSS [63].

*Diabetes distress* is measured using The Problem Areas in Diabetes questionnaire (Swe-PAID-20): This is a 20 items questionnaire translated in to Swedish by Amsberg et al. [64]. The patient rates their distress with having diabetes on a five-point Lickert scale, from 0 = not a problem to 4 = serious problem. The total score ranges from 0-100. The original version of PAID was developed by Polonsky et al., 1995 [65]. These questions are only answered by the participants diagnosed with diabetes.

